### Objectives

2.1.

Primary objective:
-To identify the barriers to establishing standardized SSI prevention practice.Secondary objectives:
-To identify intra- and inter-specialty variations in surgical site infection prevention practice.-To identify variations in practice amongst financial systems such as state and privately funded healthcare systems and economical classifications.

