### Questionnaire development

2.3.

A pilot questionnaire will be developed based on SSI prevention measures outlined in the CDC (2017), WHO (2018), NICE (2019), Wounds UK (2020) and the International Surgical Wound Complications Advisory Panel (ISWCAP) guidelines. Additionally, feedback from the survey of surgical site infection prevention practice in UK vascular surgery will be used to inform survey questions/design (12–14, 18, 19). Since the survey will be targeting participants across multiple specialties, it will only contain general prevention measures widely applicable. A draft survey will be provided in Supplementary Material 1.

The questionnaire will be structured into five sections; demographics, SSI surveillance, preoperative, peri-operative and postoperative SSI prevention domains. Data will be collected on participant surgical specialty, operative grade, country of practice and financial healthcare system of practice. SSI data will include criteria used for diagnosis. There were 15 perioperative domains formulated the UK questionnaire, which will be scrutinized against the CDC, WHO, NICE and ISWCAP guidelines outlined above by the SSC, to form a pilot questionnaire. The process of questionnaire development will be carried out through discussion by members of the SSC and a record of any question refinement will be documented. The number of questions will not be rigidly defined but the SSC will consider the impact on survey duration which can influence completion rates.

The pilot questionnaire will be distributed to at least two consultants of each surgical specialty; vascular, general, orthopedic and trauma, urology, plastic and reconstructive, cardiothoracic, neurosurgery and otolaryngology for multiple rounds of validation. After each round feedback will be analyzed by the SSC and consensus-based changes will be adopted. Any alterations will be done so on unanimous decision and documented as major (questions removed or added), and minor (wording alterations). The survey will be validated further in subsequent rounds until the SSC agrees no further alterations are required.

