### Sample characteristics

2.4.

The survey will be sent out electronically to surgeons of any specialty and at all levels of training worldwide. This includes consultants, and surgical trainees (specialties registrars/residents). To be included in the study, surgeons must be currently practicing and be registered with the national surgical body/college/society. The validated online survey will be distributed through Qualtrics^XM^ for single-stage cluster sampling in addition to dissemination through social media, where snowballing may occur. Each network of distribution will provide a cluster, i.e., VERN for the vascular surgeons and PIACO group for general surgery. The study population will provide a representation of existing SSI preventative measures used worldwide.

Given the global nature of the survey, no sample size will be calculated. Raking will be used to assign weight values to each survey respondent in such a manner, that the weighted distribution of the sample is in very close agreement with two or more marginal control variables. Socio-economic (developing vs. developed countries) variables and surgical specialties will be used to weigh the sample of responses. As such, results will be able to be extrapolated into wider populations, irrespective of the distribution of responses received.

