### Limitations

3.1.

Reminders will be sent on a 2-weekly basis to increase the response rate and to prevent sampling bias. Additionally, the study will be advertised on its own Twitter account to gain attention. Response fatigue is a common issue, leaving some questions unanswered. To keep this to a minimum, the survey has been designed to only ask relevant questions and to be succinct, clear, and unambiguous.

Due to the nature of the study, there is room for responder and recall bias. To minimize this, questions wording and survey length have been considered carefully during all steps of the development of the survey. Questions will be categorized into SSI-related preoperative, perioperative, and postoperative themes to preserve the structure and enable ease of organization for respondents to follow.

Additionally, there may be discrepancies in the response rates between different countries, not providing an accurate representation of certain regions. There may also be different local/national guidelines and unequal access to certain resources depending on the geographical regions. As this survey will be delivered worldwide, questions are based on guidelines from the National Institute for Health and Care Excellence (NICE), Centers for Disease Control and Prevention (CDC) and World Health Organization (WHO). These guidelines are internationally recognized and available, therefore discrepancies between geographical regions and differences in local guidelines should be kept to a minimum.

There is no standardized consensus recommendation on SSI prevention regarding perioperative practice. Unsurprisingly this can lead to a discrepancy in clinical practice, as shown by a questionnaire study within the UK (15). If international and pan-surgical SSI prevention practices also vary, guidance recommended by international bodies is not being followed. This may be due to the lack of underlying evidence for SSI prevention practice, and thereby the necessity for high-quality RCTs to establish the best practice for patients and surgeons worldwide.

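### Raking on specialty and a developing/developed split cannot support extrapolation whatever the response pattern, because country and grade imbalance within each weighting cell stays uncorrected

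*Protocol article*

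**What the plan says.** Section 2.4 (Sample characteristics) describes raking as giving weights such that "the weighted distribution of the sample is in very close agreement with two or more marginal control variables". It then names two variables: "Socio-economic (developing vs. developed countries) variables and surgical specialties will be used to weigh the sample of responses". From this it draws the inference: "As such, results will be able to be extrapolated into wider populations, irrespective of the distribution of responses received". The same section recruits through "single-stage cluster sampling in addition to dissemination through social media, where snowballing may occur", admits trainees as well as consultants, and calculates no sample size.

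Section 2.3 (Questionnaire development) shows that more is known about each respondent: "Data will be collected on participant surgical specialty, operative grade, country of practice and financial healthcare system of practice". Country, grade and financial system are not named as raking variables.

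The secondary objectives in section 2.1 are "To identify intra- and inter-specialty variations in surgical site infection prevention practice" and "To identify variations in practice amongst financial systems such as state and privately funded healthcare systems and economical classifications". The Abstract names a chi-square test for the analysis.

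Section 3.1 (Limitations) concedes: "Additionally, there may be discrepancies in the response rates between different countries", and adds that some regions may be poorly represented as a result.

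**The concern.** Raking corrects the sample only for the variables it uses. With two margins, one of them binary, a country that answers in large numbers keeps its excess influence within the developed or developing group. A grade that answers in large numbers keeps its excess influence everywhere. Recruitment through networks, social media and snowballing makes both likely. The Discussion also expects practice to differ between countries, and unequal response combined with unequal practice is what produces bias.

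Section 2.4 nevertheless promises that the response pattern will not matter, while section 3.1 says that it may. A reader who relies on section 2.4 would take the weighted percentages as estimates of worldwide practice when they could be several points off.

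**Working it through.** The article gives no population margins, expected response or practice rates, so there is no figure to reproduce. The check is algebra followed by illustrations. **Every numerical input below is assumed.**

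**1. Form of the weight.** Raking on specialty i and development level j gives w_ij = a_i × b_j. Nothing in w_ij depends on country or grade, so all respondents in cell (i, j) share one weight.

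**2. Bias left behind.** Suppose a subgroup has sample share s and true share t in every cell of a stratum, with practice rate p1 in the subgroup and p0 elsewhere. Then:
- raked estimate = s·p1 + (1 − s)·p0
- target = t·p1 + (1 − t)·p0
- bias = (s − t)(p1 − p0)

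**3. Country within the developed stratum.** Assume p1 = 80%, p0 = 60%, t = 10%. The target is 0.10 × 80 + 0.90 × 60 = 62%.
- s = 30%: 0.30 × 80 + 0.70 × 60 = 66%, bias +4 points
- s = 50%: 0.50 × 80 + 0.50 × 60 = 70%, bias +8 points
- s = 80%: 0.80 × 80 + 0.20 × 60 = 76%, bias +14 points

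If the developing stratum is unbiased, the overall bias is this figure times the developed share of the population. At an assumed share of 50% it is 2 to 7 points (0.5 × 4 to 0.5 × 14). At 30% it is 1.2 to 4.2 points.

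**4. Grade.** Assume 50% use among trainees, 70% among consultants, and a true trainee share of 30%. The target is 0.30 × 50 + 0.70 × 70 = 64%.
- 50% trainees in the sample: 0.50 × 50 + 0.50 × 70 = 60%, bias −4 points
- 70% trainees: 0.70 × 50 + 0.30 × 70 = 56%, bias −8 points

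**5. What the weights do to the comparisons.** Within specialty i the weighted rate is Σ a_i·b_j·y / Σ a_i·b_j = Σ b_j·y / Σ b_j. The specialty factor cancels and the development factor stays. In a developed/developing contrast the roles reverse. In a funding-system contrast neither factor cancels.

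An illustrative table has two specialties with 400/20 and 150/130 respondents (developed/developing), practice rates of 80/50% and 70/40%, and target margins of 30/70 for specialty and 40/60 for development. Raking to convergence gives:
- difference between specialties: 22.5 points unweighted (78.6% − 56.1%), 28.3 raked (74.8% − 46.5%)
- developed minus developing: 35.9 unweighted, 35.3 raked
- overall rate: 69.6% unweighted, 55.0% raked
- weighting on specialty alone: specialty rates unchanged at 78.6% and 56.1%

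For funding, assume state-funded shares of 90/30% and 60/50% in the same cells, with rates 5 points above (state) or below (private) the cell values. The state-minus-private difference moves from 23.2 to 21.5 points.

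**The case against.** Several points on the other side have force.

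- **Disclosure.** Section 3.1 already admits uneven response by country. But it does not withdraw the claim in section 2.4, so the two sections conflict. Its reassurance that the questions rest on internationally recognised guidelines concerns what is asked, not who answers.
- **Room for more margins.** The general description allows two or more, and extra margins, their sources and adjusted models may be set out in a fuller plan. Their absence from an article is therefore not the point. The point is an inference the article does state, drawn from the two margins it names.
- **The weights do useful work.** They move the overall rate substantially in the illustration, and overall figures bear on the primary objective about barriers.

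A reader might infer that the raked weights drop out of the comparisons in the secondary objectives. They do not: only the factor defining the compared groups cancels, which would happen under any raking scheme and is no defect. Full cancellation occurs only inside a single specialty-by-development cell.

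A reader might also infer that a binary split is coarser than the objective on economic classes. The article does not say how many classes it means, a raking variable need not match a comparison variable, and finer classes can still be derived from country. Leaving funding system out of the margins is likewise not a contradiction.

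**Conclusion.** The concern holds as a point about an overclaim. Raking on specialty and a developing/developed split cannot make the estimates independent of who responds, and section 3.1 names an imbalance that these margins do not remove.

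Under the assumed inputs, residual bias is about 4 to 14 points for country within a development stratum and 4 to 8 points, in absolute size, for grade. The country effect on the overall figure shrinks in proportion to the stratum's population share if only that stratum is affected. These sizes assume a similar imbalance in every cell. The mechanism does not depend on the particular values, but with no imbalance, or no difference in practice, the bias is zero.

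More extreme inputs give larger figures. A country with 60% of developed-country replies but 5% of surgeons, and use of 70% against 40% elsewhere, gives (0.60 − 0.05) × 30 = 16.5 points. That is one assumed scenario for the developed stratum alone and should not be read as the expected error. The survey can proceed, but its claim to represent worldwide practice should be limited.

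**What to change.** 1. Replace the extrapolation sentence in section 2.4 with a statement that weighting corrects only for the named margins, and make it consistent with section 3.1.
2. Derive a finer income group or region from the country already collected. Use it, and grade, as further margins only where a credible population total exists.
3. Report a leave-one-country-out sensitivity analysis for the country contributing most responses. This is needed even with finer margins, because one country can still dominate its region or income group.
4. Compare specialties and funding systems with a model adjusted for income group or region and for grade, in place of relying on the raked weights and an unadjusted chi-square test.

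The first, third and fourth changes need only wording and data already collected. The cost is a little more analysis. The second also requires a search for population totals, which may not exist, and makes the weights somewhat more variable; a cap on the weights would limit that. None of these steps removes selection on characteristics that the survey does not record.

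### Raking to the specialty and development margins leaves the recruited association between them unchanged, so specialty and economic-class contrasts still depend on who responded

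*Protocol article*

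**What the plan says.** Sample characteristics (2.4) commits to raking, with weights chosen so that "the weighted distribution of the sample is in very close agreement with two or more marginal control variables". It names the controls: "Socio-economic (developing vs. developed countries) variables and surgical specialties will be used to weigh the sample of responses". No cross-classified target is mentioned. The section then concludes that "results will be able to be extrapolated into wider populations, irrespective of the distribution of responses received".

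The same section describes recruitment: "Each network of distribution will provide a cluster, i.e., VERN for the vascular surgeons and PIACO group for general surgery", "in addition to dissemination through social media, where snowballing may occur".

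Objectives (2.1) includes, as a secondary objective, "To identify intra- and inter-specialty variations in surgical site infection prevention practice". Another secondary objective covers variation by healthcare financing and economic classification.

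Limitations (3.1) accepts that "there may be discrepancies in the response rates between different countries, not providing an accurate representation of certain regions" and that "There may also be different local/national guidelines and unequal access to certain resources depending on the geographical regions".

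The Abstract names a chi-square test for the responses. It does not say whether the test uses the weights.

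**The concern.** Raking multiplies each row and each column of the sample table by a constant until both margins reach their targets. The odds ratio between the raking variables does not change. Both margins can therefore look right while the weighted sample of one specialty comes mainly from developed countries and that of another mainly from developing countries, in a pattern set by recruitment.

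The design makes such a pattern plausible. The two networks given as examples are each tied to one specialty, and social media and snowballing add respondents whom nobody selects. The Limitations section expects uneven response by country and uneven access to resources, so practice may well differ by development status.

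At stake are the specialty and economic-class comparisons. Two specialties that practise identically within each development class could appear to differ, and a reader told that the response distribution no longer matters would take the difference as real. The same holds in reverse for economic class. The primary objective, barriers to standardised practice, is not itself a specialty contrast.

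**Working it through.** The article gives no counts, targets or practice rates, so there is no figure of its own to reproduce. All inputs below are assumptions.

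**Inputs.** Specialty A has 196 developed and 4 developing respondents; specialty B has 120 and 80. Use of a measure is 80% in developed and 50% in developing countries in both specialties, so the within-class difference is 0. The specialty target is 50/50. The developed-country target *c* runs from 10% to 90%.

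**Unweighted.**
- A: 0.98 × 80% + 0.02 × 50% = 79.4%.
- B: 0.60 × 80% + 0.40 × 50% = 68.0%.
- Gap: 11.4 points.

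**Raked.** Let *a* and *b* be the weighted developed shares in A and B. Two conditions fix them:
- development margin with equal specialty weights: *a* + *b* = 2*c*
- unchanged odds ratio: [*a*/(1 − *a*)] / [*b*/(1 − *b*)] = (196 × 80)/(4 × 120) = 32.67

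The gap is then (*a* − *b*) × (80% − 50%). At *c* = 50%, *b* = 1 − *a*, so *a*/(1 − *a*) = √32.67 = 5.716 and *a* = 0.851, *b* = 0.149. Weighted use is 75.5% against 54.5%, a gap of 0.702 × 30 = 21.1 points. Iterative proportional fitting gives the same result, with the odds ratio still 32.67.

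| Developed target | Developed share, A | Developed share, B | Raked gap (points) |
|---|---|---|---|
| 10% | 19.3% | 0.7% | 5.6 |
| 20% | 38.1% | 1.9% | 10.9 |
| 30% | 56.2% | 3.8% | 15.7 |
| 50% | 85.1% | 14.9% | 21.1 |
| 70% | 96.2% | 43.8% | 15.7 |
| 80% | 98.1% | 61.9% | 10.9 |
| 90% | 99.3% | 80.7% | 5.6 |

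The sample is (196 + 120)/400 = 79% developed. At a 79% target raking changes nothing and the gap stays at 11.4. The gap is symmetric about 50%, so here it widens for targets between 21% and 79% and narrows outside that range.

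**Milder imbalance, same rates.**
- 190/10 against 140/60: odds ratio 8.14; unweighted gap 7.5; raked 14.4 at a 50% target and 4.5 at 10% or 90%.
- 180/20 against 150/50: odds ratio 3.00; unweighted gap 4.5; raked 8.0 at 50% and 2.8 at 10% or 90%.

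**Reverse contrast.** Take the first table and let practice differ by specialty only (A 80%, B 50%).
- Developed: (196 × 80% + 120 × 50%)/316 = 68.6%.
- Developing: (4 × 80% + 80 × 50%)/84 = 51.4%.
- The unweighted gap is 17.2 points; raked to 50/50 on both margins it is 21.1.

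**How general is widening?** In 20,000 randomly drawn 2 × 2 settings, raking widened the specialty gap in about 39%. Where the sample was over 70% developed and above its target, it did so in about 76%. These fractions depend on the ranges drawn and show only that both directions are common.

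**With standardisation.** If both specialties are weighted to the same developed share, say 50%, each gives 0.5 × 80% + 0.5 × 50% = 65%, and the gap is 0.

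**The case against.** The strongest reply is that the article nowhere says the specialty comparisons or the chi-square tests use the raked weights, or that specialties are compared without regard to development status. Raking appears under sample characteristics, and the details of a contrast may sit in a fuller document. This stands as a limit: a reader might infer that the planned comparisons are weighted this way, and the text does not establish it. It does not remove the point. The extrapolation sentence covers results generally, and an unweighted specialty comparison is also confounded by country mix (11.4 points in the example).

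Other objections stand in part:

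- The phrase about two or more controls leaves room for a joint one. The sentence naming the controls lists only the two variables.
- The article gives no country reach for any network, so strong specialty-by-development imbalance is plausible but assumed.
- A reader might infer that raking preserves the recruited mix itself. It does not: the developed shares move from 98% and 60% to 85% and 15% at a 50% target. Only the association is preserved.
- A reader might also infer that raking generally doubles the false gap. The near-doubling is at the 50% target, where the gap peaks; at 20% or 80% it is 10.9 points, below the unweighted 11.4.
- If specialties truly differ in development mix worldwide, part of a summed contrast is real, and equal-mix weighting answers a different question. Labelling the result as standardised, or using joint population totals where they exist, meets this.

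**Conclusion.** The point holds as a limit on what margin raking can deliver. With the two named controls and no joint one, the recruited association passes unchanged into the weighted data. The claim that the response distribution ceases to matter is therefore wrong for the specialty and economic-class contrasts.

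A summed specialty contrast is distorted under two conditions: practice differs by development status, and the recruited association differs from the population's. The article makes both plausible and quantifies neither. In the example, the whole gap is artefact only if specialty and development status are unrelated in the population; otherwise the artefact is the departure from the population's own gap. The range of 5.6 to 21.1 points against 11.4 unweighted shows that weighting can move the gap either way. It does not predict this survey's results.

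The matter affects secondary objectives and should be corrected before analysis.

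**What to change.** In section 2.4:

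1. Keep raking to the two margins for the overall figure.
2. For comparisons between specialties, standardise each specialty to a common development mix, such as the overall control share, or compare within development class. For comparisons between economic classes, standardise each class to a common specialty mix. Label both as standardised.
3. If specialty-by-development population totals exist, post-stratify to them for population-level contrasts.
4. Where a specialty has too few respondents in one class, compare within the other class only.
5. Delete the statement that results extrapolate whatever the response distribution, or restrict it to what the controls can support.

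Specialty and country are already collected (Questionnaire development, 2.3), and step 2 needs no new population totals. The work is a wording change and a few lines of weighting code.

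The price is larger weights and wider intervals in sparse cells. In the example, standardising specialty A to 50% developed gives its 4 developing-country respondents a weight of 0.50/0.02 = 25 each and the other 196 a weight of 0.50/0.98 = 0.51. The effective sample size is 200²/(4 × 25² + 196 × 0.51²), about 16 of 200. This is why step 4 is needed.

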**Methods:**

This collaborative cross-sectional survey will be aimed at pan-surgical specialties internationally. The study has been designed and will be reported in line with the CROSS and CHERRIES standards. An international study steering committee will design and internally validate the survey in multiple consensus-based rounds. This will be based on SSI prevention measures outlined in the CDC (2017), WHO (2018), NICE (2019), Wounds UK (2020) and the International Surgical Wound Complications Advisory Panel (ISWCAP) guidelines. The questionnaire will include demographics, SSI surveillance, preoperative, peri-operative and postoperative SSI prevention. Data will be collected on participants' surgical specialty, operative grade, of practice and financial healthcare system of practice. The online survey will be designed and disseminated using Qualtrics^XM^ Platform™ through national and international surgical colleges and societies, in addition to social media and snowballing. Data collection will be open for 3 months with reminders, and raking will be used to ascertain the sample. Responses will be analyzed, and the chi-square test used to evaluate the impact of SSI prevention variables on responses.

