### Survey administration

2.5.

The survey will be advertised in weekly rounds, 1 month prior to dissemination using affiliated society social media accounts and the Surgical Infection Research Network Twitter account (@SIRNglobal).

The survey will be disseminated worldwide, with an international SSC to establish a network of distribution. The committee has been involved in previous successful surveys and collaborative projects through the PIACO group, the Vascular Endovascular Research Network (VERN), James Lind Alliance (JLA) and ISWCAP surveys (20–23). The committee will also identify new routes of distribution within this project. The validated online survey will be distributed using an electronic link. Participants will receive an email via their affiliated membership organization, inviting them to take part and will include a direct link to the online survey. Following the invitation, surgeons will have 3 months to complete the survey, with reminders sent every 2 weeks. The survey will also be promoted via social media platforms, using the SIRN Twitter account in addition to affiliated organization accounts. The “prevent multiple submissions” option in Qualtrics will be enabled to prevent multiple participation of participants. A secondary IP address check will follow to ensure there are no remaining duplicate entries. No two entries from the same IP address will be allowed within 24 h. After the data collection window, the survey will lock out, preventing further responses. Participants will be offered an opportunity to win a £20 Amazon voucher as an incentive to participate in the survey. Survey items will not be randomized to improve participation, as the logical order of each survey section was unanimously agreed by the SSC to improve the response flow. Adaptive questioning will be used depending on the following questions from a response. The number of items and screens or pages on mobile and personal computers will be reported in the manuscript write-up.

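### Raking on development status and specialty cannot make results generalisable whatever the pattern of responses

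*Protocol article*

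**What the plan says.** Section 2.4 (Sample characteristics) describes raking as giving weights such that "the weighted distribution of the sample is in very close agreement with two or more marginal control variables". It then names the variables: "Socio-economic (developing vs. developed countries) variables and surgical specialties will be used to weigh the sample of responses". From this it concludes: "As such, results will be able to be extrapolated into wider populations, irrespective of the distribution of responses received".

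The same section describes recruitment as "single-stage cluster sampling in addition to dissemination through social media, where snowballing may occur". Section 2.5 (Survey administration) adds invitations through membership organisations, promotion on the account of a surgical infection research network, and a prize draw: "Participants will be offered an opportunity to win a £20 Amazon voucher as an incentive to participate in the survey".

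Section 3.1 (Limitations) says that "there may be discrepancies in the response rates between different countries, not providing an accurate representation of certain regions". It also accepts that responder bias is possible.

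**The concern.** The sentence asserts a property of the method, so it cannot be excused as detail left to a fuller document. Raking makes the weighted sample match chosen totals. It carries no information about how responders differ from non-responders inside a category. Surgeons with an interest in wound infection may be more likely to answer and also more likely to use preventive measures. If so, weighting by specialty and development status leaves that difference in place.

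The words about the distribution of responses also fail mechanically, because raking depends on who replies. At stake is whether percentages from volunteers are reported as the practice of surgeons worldwide, which section 2.4 says the study population will represent. A reader would also not see how much precision the weights had cost.

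**Working it through.** The article gives no sample size, precision target, population margins or expected response pattern, so there is no figure of its own to reproduce. All inputs below are assumptions chosen to show a range.

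**1. Self-selection within weighting cells.** Let p be the true proportion using a measure, and let users be r times as likely to respond as non-users in every cell. With p the same in every cell, the estimate after perfect raking is p·r / (p·r + 1 − p).

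| True p | r = 1 | r = 1.25 | r = 1.5 | r = 2 |
|---|---|---|---|---|
| 50% | 50.0% | 55.6% | 60.0% | 66.7% |
| 30% | 30.0% | 34.9% | 39.1% | 46.2% |

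For example, with p = 0.5 and r = 1.5: 0.75 / (0.75 + 0.5) = 0.60. The number of replies does not enter the formula, so a larger survey does not reduce the bias.

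**2. What raking does and does not remove.** Take a table of 2 development classes by 8 specialties, with the classes 50/50 in the population. Use of the measure differs by class and specialty. Response differs fivefold between classes and up to sixfold between specialties. Iterative proportional fitting met the class margin exactly (0.5/0.5) in all three cases. The true value is 48.4%.

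| r within cells | Unweighted | Raked | Remaining error of raked estimate |
|---|---|---|---|
| 1 | 52.7% | 48.4% | 0 |
| 1.5 | 62.5% | 57.9% | 57.9 − 48.4 = 9.5 points |
| 2 | 69.0% | 64.4% | 64.4 − 48.4 = 16.0 points |

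Raking removes the imbalance on its margins and brings the estimate closer to the truth in every row. It does not remove self-selection within cells. The exact recovery at r = 1 is helped by the example having no class-by-specialty interaction in response or practice.

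**3. Dependence on the distribution received.** For one binary margin, let P be the population share and s the sample share of developing countries. Kish's effective sample size as a fraction of n is 1 / (P²/s + (1 − P)²/(1 − s)).

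- P = 0.5, s = 0.4: 1 / (0.625 + 0.417) = 0.96
- P = 0.5, s = 0.2: 1 / (1.25 + 0.3125) = 0.64
- P = 0.6, s = 0.2: 1 / (1.8 + 0.2) = 0.50
- P = 0.6, s = 0.1: 1 / (3.6 + 0.178) = 0.265

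So 1,000 replies could carry the information of 960, 640, 500 or 265, depending on who answers. With s = 0 the weight P/s is undefined and that category cannot be raked.

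**4. The two sections side by side.** Section 2.4 makes extrapolation independent of the responses received. Section 3.1 says uneven response by country may leave some regions inaccurately represented. A two-level development variable cannot correct imbalance between countries within the same level. Country, grade and funding system are collected (section 2.3) but are not named as margins, although variation between funding systems is a secondary objective (section 2.1).

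**The case against.** Raking is a reasonable step, and part 2 of the working shows that it helps. The Limitations section already admits responder bias and weak regional coverage, so readers are partly warned. The objectives concern barriers and variation between specialties and funding systems, not a worldwide prevalence. These points temper the consequence. They do not make the sentence true, and section 2.4 does say that the sample will represent measures in use worldwide.

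The label of cluster sampling does not rescue the claim either, since social media and snowballing are open routes by design.

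Some stronger readings are tempting but are not supported:

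- **That raking is the reason for doing without a sample size.** The stated reason is different: "Given the global nature of the survey, no sample size will be calculated". That sentence comes before raking is mentioned, and the extrapolation sentence refers back only to the weighting.
- **That sections 2.4 and 3.1 flatly contradict each other.** Section 3.1 speaks of what may happen in certain regions, and the weights are not by region. Estimates adjusted for the named margins could coexist with weak regional coverage. The tension lies in the unconditional wording.
- **That the abstract repeats the claim.** Its phrase "raking will be used to ascertain the sample" is loose but says nothing about extrapolation.
- **That the article is deficient for lacking weight caps or minimum cell counts.** Such rules commonly belong in an analysis plan, and their absence here is no fault.

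**Conclusion.** The concern holds as a matter of overstated inference. The article claims for raking a generality that it does not have in a survey of volunteers. The method itself is acceptable; the unconditional conclusion drawn from it is not.

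The size cannot be known from the article. With a true 50% and response ratios of 1.25 to 2, the bias left after raking is about 6 to 17 percentage points. With a ratio of 1 there is none from this source. The ratios and population shares are assumptions, so a reader should not infer that the survey's estimates will be wrong by any particular amount. The assumptions show only that the claim fails under moderate self-selection, and that precision varies with the responses received.

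**What to change.** - In section 2.4, delete the clause that makes extrapolation independent of the distribution of responses.
- State instead that raked results adjust only for development status and specialty (and any further margin actually used), and that they remain subject to self-selection. Align this with section 3.1.
- Report unweighted and raked estimates side by side, with the effective sample size after weighting.

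The cost is a few words in the protocol and a few lines of analysis code. The downside is a more modest claim of generalisability.
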